**Motor Recovery**

***Fugl-Meyer Assessment***

The Fugl-Meyer assessment[^38^](#_ENREF_38) (FMA) is a performance-based measure. It has five sections to test a specific construct (motor, balance, sensation, range of motion and pain). The motor section of FMA is arranged hierarchically and evaluates aspects of movement, reflexes, coordination, and speed. The motor section is further divided into two subsections; the upper extremities (upper arm and wrist and hand) and lower extremities. The upper extremity (FMA-UE) subsection will be used to assess upper extremity recovery in the present study. It is scored out of 66, with sub-score of 36 for the upper arm (FMA-UA) and 30 for the wrist and hand (FMA-WH). Most of the items are scored on a 3-point ordinal scale; from 0 – no function to 2 – full function. The lower-extremity subsection (FMA-LE) comprised items ranging from reflexes, synergy, combining synergies, out of synergy, and coordination. FMA-LE has a total of 17 items, which are scored on a 3-point ordinal scale (0 [no performance] to 2 [full performance]). The FMA has been found to be a highly reliable (r = 0.98–0.99) and valid (r = 0.61–0.94) tool to assess the motor recovery of post stroke patients.[^44-46^](#_ENREF_44)

**Secondary measures**

- - 1. ***Catherine Bergego Scale***

The Catherine Bergego Scale (CBS) is used to measure neglect. It is a valid, reliable, and sensitive measure of poststroke neglect. Specifically, it has good internal consistency, inter-rater reliability, concurrent validity and convergent validity. The CBS is a functional neglect assessment because it assesses neglect through observation of activities such as eating and locomotion (i.e. collisions, navigation items). The CBS has items that assess for personal, peripersonal, and extrapersonal neglect and the type of neglect each item assesses has been delineated. Assessors score 10 items using a 4-point scale. Higher CBS scores (range: 0-30) indicate more severe neglect. Kessler Foundation Neglect assessment Process guidelines will be used to apply the CBS.[^47^](#_ENREF_47)^,^ [^48^](#_ENREF_48)

- - 1. ***Berg Balance Scale***

The Berg Balance Scale (BBS) has been developed to measure balance among older people with impairment in balance function by assessing the performance of functional tasks. It is a valid instrument used for evaluation of the effectiveness of interventions and for quantitative descriptions of function in clinical practice and research.[^49^](#_ENREF_49) It is a commonly used measure to assess balance ability among post-stroke subjects.[^50^](#_ENREF_50) It is a 14-item measure, items ranging from sit-to-stand to standing on one foot. All the items are score on 0 to 4, 4 being the positive performance. The total score is 56, with < 40 and < 20 being considered as medium and high fall risk, respectively for the subject.

- - 1. ***Functional Ambulation Category (FAC)***

Functional Ambulation Category (FAC) measures the walking ability of the poststroke subjects. It is an economical and simple method to quantify independency in ambulation. The scale defines 6 categories ranging from 0 (unable to walk) to 5 (independent walking). FAC has exhibited acceptable reliability and validity.[^51^](#_ENREF_51)^,^ [^52^](#_ENREF_52)

- - 1. ***Modified Rankin scale***

The modified Rankin scale (mRS) is a clinician-reported and recommended measure of global disability.[^53^](#_ENREF_53) It is widely used for evaluating trial outcomes of stroke patients and is an end point in randomized clinical trials.[^54^](#_ENREF_54) mRS scores range from 0 (no symptoms at all) to 5 (severe disability)

*Distribution of Outcome measure as per International classification of Functioning (ICF)*

| **Outcome Measure** | **Level of Measure**  (International Classification of Functioning) |
| --- | --- |
| Line Bisection Test (LBT)  Letter Cancellation Test (LCT) | Spatial ability **(Body function)** |
| Fugl-Meyer assessment (FMA) | Motor recovery **(Body function)** |
| Catherine Bergego Scale | Spatial related functions **(Activity)** |
| Berg Balance Scale | Balance **(Activity)** |
| Functional Ambulation Classification (FAC) | Ambulation **(Activity)** |
| Modified Rankin Scale (mRS) | Disability **(Participation)** |

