**Secondary objectives**

- 1. To determine the effectiveness of the Task-based and Magnified mirror therapy on functional performance of the subjects
  2. To determine the effectiveness of the protocol on disability status among the subjects.

1. **Methodology:**

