**Inclusion Criteria:**

- Age: 20 to 80 years
- Both male & female
- First episode of unilateral stroke (as defined by WHO)
- Ischemic or hemorrhagic stroke
- 1 to 36 months after the stroke onset
- Hemiparesis (right or left) (as assessed by Fugl-Meyer assessment[^38^](#_ENREF_38) upper extremity subsection: 0 to 66)
- USN (defined as an asymmetry between the Letter cancellation task omissions in the contralesional (left) and ipsilesional (right) visual field of at least 2 letters)[^33^](#_ENREF_33)
- Normal visual abilities (with or without glasses)
- Muscle tone: Modified Ashworth scale 1 to 2

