**SPIRIT Guidelines**

|  | **STUDY PERIOD** | | | | |
| --- | --- | --- | --- | --- | --- |
|  | **Enrolment** | **Allocation** | **Intervention** | | **Follow-up** |
| **TIMEPOINT** | ***-t_1_*** | **0** | ***t_1_*** | ***t_2_*** | ***t_3_*** |
| **ENROLMENT:** |  |  |  |  |  |
| **Eligibility screen** | X |  |  |  |  |
| **Informed consent** | X |  |  |  |  |
| ***Randomization*** |  | X |  |  |  |
| **Allocation** |  | X |  |  |  |
| **INTERVENTIONS:** |  |  |  |  |  |
| ***[Task-based & Magnified Mirror Therapy]*** |  |  |  |  |  |
| ***[Control]*** |  |  |  |  |  |
| **ASSESSMENTS:** |  |  |  |  |  |
| ***[Demographic Information]*** |  | X |  |  |  |
| ***[Patient Characteristic]*** |  | X |  |  |  |
| ***[Standard Neuro-Rehab. Clinical Evaluation]*** |  | X |  |  |  |
| ***LCT*** | X |  |  | X | X |
| ***LBT*** |  |  | X | X | X |
| ***FMA*** |  |  | X | X | X |
| ***CBS*** |  |  | X | X | X |
| ***BBS*** |  |  | X | X | X |
| ***FAC*** |  |  | X | X | X |
| ***mRS*** |  |  | X | X | X |

T1 baseline assessment, T2 assessment after 8 weeks of intervention, T3 assessment after four-week follow-up (12 weeks after start of intervention). LCT = Letter Cancellation Task, LBT = Line Bisection Test, FMA = Fugl-Meyer assessment, CBS = Catherine Bergego Scale, BBS = Berg Balance Scale, FAC = Functional Ambulation Category, mRS= modified Rankin scale

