**Data Analysis:**

The data will be analyzed by using IBM SPSS version 23.0. The demographic and baseline features of the study participants will be analyzed in form of mean (SD) / median (IQR) / n (%) and appropriate test [(Mann-Whitney U (U) / independent t (t) / chi-square (χ^2^)] tests will be used to analyze the difference for the characteristics between the groups. For inferential statistics, an intention-to-treat analysis method will be used by carrying forward the last observation. A repeated-measures 2-way ANOVA (continuous data; within factor, time; between factor, group) will be used to study difference for the post intervention and follow-up scores between the groups. The pre-intervention score will be considered as the covariate with group as the independent variable and posttest score as the dependent variable. The significance level will be set at *P*<.05. The dummy tables to represent the findings are provided below -

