| **Outcome measure** | **Pre-intervention** | |  | **Post-intervention** | |  | **Follow-up** | | |
| --- | --- | --- | --- | --- | --- | --- | --- | --- | --- |
|  | **Experimental Group (n=43)** | **Control Group (n=43)** | **Test**  **Statistics** | **Experimental Group (n=43)** | **Control**  **Group (n=43)** | **Test**  **Statistics** | **Experimental Group (n=43)** | **Control**  **Group (n=43)** | **Test**  **Statistics** |
| FAC 0 *– n (%)* |  |  | χ^2^:p = |  |  | χ^2^:p = |  |  | χ^2^:p = |
| FAC 1*– n (%)* |  |  |  |  |  |  |  |  |  |
| FAC 2*– n (%)* |  |  |  |  |  |  |  |  |  |
| FAC 3*– n (%)* |  |  |  |  |  |  |  |  |  |
| FAC 4*– n (%)* |  |  |  |  |  |  |  |  |  |
| FAC 5*– n (%)* |  |  |  |  |  |  |  |  |  |

n – Number

**Table 8: Changes in Pre- and Post-intervention, and Follow up scores of Modified Rankin Scale (mRS) between the experimental and control groups**

| **Outcome measure** | **Pre-intervention** | |  | **Post-intervention** | |  | **Follow-up** | | |
| --- | --- | --- | --- | --- | --- | --- | --- | --- | --- |
|  | **Experimental Group (n=43)** | **Control Group (n=43)** | **Test**  **Statistics** | **Experimental Group (n=43)** | **Control**  **Group (n=43)** | **Test**  **Statistics** | **Experimental Group (n=43)** | **Control**  **Group (n=43)** | **Test**  **Statistics** |
| mRS 0 *– n (%)* |  |  | χ^2^:p = |  |  | χ^2^:p = |  |  | χ^2^:p = |
| mRS 1*– n (%)* |  |  |  |  |  |  |  |  |  |
| mRS 2*– n (%)* |  |  |  |  |  |  |  |  |  |
| mRS 3*– n (%)* |  |  |  |  |  |  |  |  |  |
| mRS 4*– n (%)* |  |  |  |  |  |  |  |  |  |
| mRS 5*– n (%)* |  |  |  |  |  |  |  |  |  |

n – Number

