**Ethical Consideration:**

For this study, the approval will be sought from the Institutional ethics committee (IEC) of *Pt. Deendayal Upadhya National Institute for Persons with Physical Disabilities, New Delhi, India.* The trial will comply with the principles of the “declaration of Helsinki.” Before the start of participation in this study, written informed consent will be obtained. All data collected during this study will be confidential but with open access for investigators / research staff at the study site. To protect the privacy of the participants, they will be given unique numerical codes. The key to this code will be maintained securely and confidentially by the principal Investigator. No information with which the participant can be identified will be available in any other study-related (electronic) document. All assessment forms, reports, and other (electronic) records will be coded and handled to maintain strict participant confidentiality.

The participants may withdraw from the study at any time without giving an explanation and without any negative consequences for their care or rehabilitation in the future. Based on our previous studies,[^24^](#_ENREF_24)^,^ [^34^](#_ENREF_34)^,^ [^35^](#_ENREF_35) the judgment is that there is no or very low risk of adverse events in this proposed investigation. If any adverse event is observed during the protocol, the same will be reported to the IEC and described in the dissemination of the work.

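### For the mRS, the 0–5 scale, the fixed n=43 and the unqualified carry-forward rule together count a participant who dies at the last living grade; the effect is probably small and cheap to fix

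*Protocol*

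**What the plan says.** One of the Protocol's two secondary objectives is "To determine the effectiveness of the protocol on disability status among the subjects". In the table that sorts outcome measures by ICF level, the mRS is the only measure assigned to disability.

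Four statements bear on how a death would be handled:

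- **Scale** (Secondary measures): "mRS scores range from 0 (no symptoms at all) to 5 (severe disability".
- **Table** (dummy Table 8): it is titled "Changes in Pre- and Post-intervention, and Follow up scores of Modified Rankin Scale (mRS) between the experimental and control groups". Its rows are grades 0 to 5 and nothing else. It shows a chi-square at pre-intervention, post-intervention and follow-up, and every column carries the full arm, for example "Experimental Group (n=43)".
- **Missing values** (Data Analysis): "an intention-to-treat analysis method will be used by carrying forward the last observation". No exception is given.
- **Timing** (notes to the SPIRIT schedule): T2 follows 8 weeks of intervention, and "T3 assessment after four-week follow-up (12 weeks after start of intervention").

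The methods do not name a participant's death as an outcome, a category or an exception. The nearest text is under Ethical Consideration. It expects that "there is no or very low risk of adverse events in this proposed investigation", and says that any adverse event will go to the ethics committee and be described when the work is disseminated.

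**The concern.** Death is not a missing disability score. Its value is known, and it is worse than every grade listed. A method that fills gaps with a grade from 0 to 5 must give a dead participant a living grade, so replacing carry-forward with a better imputation model would not help. What is missing is a category for death and an exemption from imputation.

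Two things are at stake. Table 8 could report as living, in a stated grade, people who have died. And if deaths fell unevenly, the arm with more of them would look better on disability than it was. The population makes the case possible: the age range reaches 80 years and entry is allowed "1 to 36 months after the stroke onset".

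**Working it through.** **1. The denominator.** The Sample size section takes 37 per group and adds 15% for drop-out: 37 × 1.15 = 42.55, rounded to 43. This reproduces the 43 in Table 8. The plan therefore allows for 43 − 37 = 6 participants per arm without complete data, and the carry-forward rule covers all of them. Deaths would be some part of those.

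**2. Tracing a death through the stated rules.**

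| Time of death | Last mRS on record | Entry at T2 (week 8) | Entry at T3 (week 12) |
|---|---|---|---|
| Between T1 and T2 | T1 grade | T1 grade, carried forward | T1 grade, carried forward |
| Between T2 and T3 | T2 grade | T2 grade, observed | T2 grade, carried forward |

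The column total stays at 43 and the only rows are 0 to 5, so no other cell is available. A death before T2 appears as unchanged from baseline at both later assessments.

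**3. Size per death.** With d deaths in one arm, the misplaced share is d/43:

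- 1/43 = 2.3%
- 2/43 = 4.7%
- 3/43 = 7.0%
- 4/43 = 9.3%
- 6/43 = 14.0% (the arm's whole drop-out allowance)

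**4. Effect on the chi-square.** The Protocol gives no mRS distribution, so this step is an illustration. Assume that both arms have counts 0, 5, 10, 16, 9, 3 in grades 0 to 5 (sum 43), that all d deaths fall in one arm, and that each had a last living grade of 4.

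- Under carry-forward the two arms are identical, so chi-square = 0 and p = 1.00.
- With death as its own category, grade 4 holds 9 against 9 − d, and died holds 0 against d. Grade 4 contributes 2 × (d/2)² / ((18 − d)/2) = d²/(18 − d). Died contributes 2 × (d/2)² / (d/2) = d. Hence chi-square = d + d²/(18 − d). Six categories are occupied, so there are 5 degrees of freedom.

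| Deaths d, all in one arm | Chi-square | p, death as own category | p, carry-forward |
|---|---|---|---|
| 1 | 1 + 1/17 = 1.06 | 0.96 | 1.00 |
| 2 | 2 + 4/16 = 2.25 | 0.81 | 1.00 |
| 3 | 3 + 9/15 = 3.60 | 0.61 | 1.00 |
| 4 | 4 + 16/14 = 5.14 | 0.40 | 1.00 |
| 6 | 6 + 36/12 = 9.00 | 0.11 | 1.00 |

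Expected counts in the died row are only d/2 per arm, so these p-values are rough. They show the order of the effect and no more.

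**5. How many deaths.** The Protocol gives no rate. If 1% to 5% died within 12 weeks (an assumption), the expected number over both arms would be 86 × 0.01 = 0.86 to 86 × 0.05 = 4.3.

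**The case against.** The best defence is that the Protocol is silent on death and that silence is not a rule. Carry-forward was presumably written with drop-outs in mind, a dummy table is a shell that can gain a row, and the handling of death is often left to the statistical analysis plan. It is true that the Protocol nowhere says in terms that a dead participant keeps a grade; that is an inference. But the Protocol has itself fixed the range, the rows, the denominators and the imputation rule. An analysis plan that followed it would produce the wrong entry, and one that avoided it would have to depart from it. Nor does it help that carry-forward is introduced for inferential statistics, because Table 8 puts the counts and the test on the same 43 per arm.

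A second defence is that a death would be disclosed anyway, through adverse-event reporting and the commitment to CONSORT. It probably would be, but neither changes the coding of the mRS.

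The third defence concerns size, and it largely stands. Follow-up is 12 weeks. Entry excludes concomitant medical illness, cardiovascular instability and renal infection or failure. Participants must be able to attend 40 two-hour sessions.

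A reader might also draw three stronger conclusions that the documents do not support:

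- **That the disability conclusion would be reversed.** In the illustration above, even four deaths all in one arm leave p far from 0.05, and an arm is favoured only if deaths are unbalanced.
- **That the Functional Ambulation Category is equally wrong without a death row.** Its table has the same structure, but it grades walking ability. A death row there is a matter of preference.
- **That nothing at all should be carried past death, for any outcome.** That would leave the line bisection, letter cancellation, Fugl-Meyer, Catherine Bergego and Berg scores with no value and no replacement rule.

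**Conclusion.** The point holds for the mRS. The Protocol's own rules leave a participant who dies only one place in Table 8, a living grade, and that entry is wrong whatever the number of deaths. The main harm is a false category count and a death scored as no worsening; a changed test result is unlikely. The measure is secondary, and the effect is 2.3 percentage points of an arm per death. The number of deaths is unknown, and the p-values rest on an assumed mRS distribution and an assumed last grade. If nobody dies, nothing is affected. The correction is worth making because it is cheap and has to be fixed before the data are seen.

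**What to change.** 1. In Table 8, add a died row below grade 5, and say under Secondary measures that death is the worst mRS outcome. The columns still sum to 43.
2. In Data Analysis, add that the mRS is not carried forward past death: a participant who has died is entered as died at each later assessment.
3. Report deaths by arm and by assessment.
4. For the Functional Ambulation Category and the continuous scales, give the number of deaths beside each table and state that values carried forward past death are not presented as observed outcomes. A death row for the walking scale is optional.

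The cost is one row, two or three sentences, and a field for vital status. That field is new work: the Protocol describes assessments at T2 and T3 but no check on participants who miss them, and participants may withdraw without giving a reason. The disability result will also look slightly less favourable in an arm with deaths.

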**Data Collection:**

The data will be collected using the assessment proforma provided as ***Annexure I.*** The proforma comprises items/questions related to demographic aspects of the subjects such as age, gender, type of stroke, duration of stroke, area of involvement, functional performance. Additionally, the clinical evaluation of a standard neuro-rehabilitation condition will also be covered. All the standardized outcome measures in form of data collecting tool have been provided in the ***Annexure II to VII.***

The flow of study process and schedule of enrolment, intervention, and assessment (SPIRIT guidelines[^55^](#_ENREF_55)) are provided below –

Post- stroke patients (1 to 36 months) – Screened for the eligibility (n=….)

Block Randomization (n=86)

Conventional Rehabilitation –

4 weeks

Experimental intervention (n=43)

(Task-based & Magnified Mirror Therapy) + Conventional Rehabilitation

40 sessions, 2 hours each during 8 weeks

Control Intervention (n=43)

(Conventional Rehabilitation)

Dose matched for duration

40 sessions, 2 hours each during 8 weeks

Enrolment

Allocation

Follow-up

Post intervention Assessment (T2)

Baseline Assessment (T1)

Follow up Assessment (T3)

**Study Flow Diagram**

Schedule of enrolment, interventions, and assessment –

**SPIRIT Guidelines**

|  | **STUDY PERIOD** | | | | |
| --- | --- | --- | --- | --- | --- |
|  | **Enrolment** | **Allocation** | **Intervention** | | **Follow-up** |
| **TIMEPOINT** | ***-t_1_*** | **0** | ***t_1_*** | ***t_2_*** | ***t_3_*** |
| **ENROLMENT:** |  |  |  |  |  |
| **Eligibility screen** | X |  |  |  |  |
| **Informed consent** | X |  |  |  |  |
| ***Randomization*** |  | X |  |  |  |
| **Allocation** |  | X |  |  |  |
| **INTERVENTIONS:** |  |  |  |  |  |
| ***[Task-based & Magnified Mirror Therapy]*** |  |  |  |  |  |
| ***[Control]*** |  |  |  |  |  |
| **ASSESSMENTS:** |  |  |  |  |  |
| ***[Demographic Information]*** |  | X |  |  |  |
| ***[Patient Characteristic]*** |  | X |  |  |  |
| ***[Standard Neuro-Rehab. Clinical Evaluation]*** |  | X |  |  |  |
| ***LCT*** | X |  |  | X | X |
| ***LBT*** |  |  | X | X | X |
| ***FMA*** |  |  | X | X | X |
| ***CBS*** |  |  | X | X | X |
| ***BBS*** |  |  | X | X | X |
| ***FAC*** |  |  | X | X | X |
| ***mRS*** |  |  | X | X | X |

T1 baseline assessment, T2 assessment after 8 weeks of intervention, T3 assessment after four-week follow-up (12 weeks after start of intervention). LCT = Letter Cancellation Task, LBT = Line Bisection Test, FMA = Fugl-Meyer assessment, CBS = Catherine Bergego Scale, BBS = Berg Balance Scale, FAC = Functional Ambulation Category, mRS= modified Rankin scale

**Data Analysis:**

The data will be analyzed by using IBM SPSS version 23.0. The demographic and baseline features of the study participants will be analyzed in form of mean (SD) / median (IQR) / n (%) and appropriate test [(Mann-Whitney U (U) / independent t (t) / chi-square (χ^2^)] tests will be used to analyze the difference for the characteristics between the groups. For inferential statistics, an intention-to-treat analysis method will be used by carrying forward the last observation. A repeated-measures 2-way ANOVA (continuous data; within factor, time; between factor, group) will be used to study difference for the post intervention and follow-up scores between the groups. The pre-intervention score will be considered as the covariate with group as the independent variable and posttest score as the dependent variable. The significance level will be set at *P*<.05. The dummy tables to represent the findings are provided below -

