**Sample size:**

The power calculation was done using the values *(Box 1)* for USN assessment from a study on mirror therapy for USN.[^27^](#_ENREF_27) Considering the beta = 0.1 and α = 0.05, the calculation inferred that 37 subjects in each group would be sufficient to detect the desired change. However, to compensate possible drop outs (15%), 43 subjects in each group will be enrolled. Thus, the total sample size will be **86**.

*Box 1*

| Study | Primary measure | Values used | Alpha | Beta | Estimated sample size each group | Total sample size |
| --- | --- | --- | --- | --- | --- | --- |
| *Pandian JD et al*[*^27^*](#_ENREF_27) | Line Bisection Test | Mean difference = 8.6  SD = 10.6 | 0.05 | 0.1 | 37 | 74 |

**Group Allocation and Concealment:** The subjects will be randomly allocated between the experimental and control groups in block of 10. The assessor will be unaware about the group allocation of the subjects and will apply the outcome measures both pre- and post intervention. The randomization process will be conducted by an office staff, not associated with the study, using the SPSS Version 23 software. The intervention will be allocated in the ratio of 1:1. The assignment will be serially arranged in sealed opaque envelopes. The subjects will also be blinded to the purpose of the experimental intervention.

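### Last observation carried forward as the only missing-data method dilutes a true effect under equal dropout and can bias the comparison either way under unequal dropout

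*Protocol*

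**What the plan says.** The Data Analysis section ties intention-to-treat to one imputation rule: "an intention-to-treat analysis method will be used by carrying forward the last observation". It applies to all inferential statistics. No assumption about why data are missing and no sensitivity analysis is stated. The model is a repeated-measures two-way ANOVA on the post-intervention and follow-up scores, with the pre-intervention score as covariate.

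The Sample size section expects losses: "to compensate possible drop outs (15%), 43 subjects in each group will be enrolled". The schedule under SPIRIT Guidelines gives the measurement times: "T1 baseline assessment, T2 assessment after 8 weeks of intervention, T3 assessment after four-week follow-up". The Intervention section lists two pre-intervention assessments, one post-intervention and one follow-up, so nothing is measured during the eight weeks of treatment. The dummy tables show 43 per group at every visit.

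Both arms are treated for 40 sessions of two hours, and the control arm also receives neglect-specific activities (Control intervention). The Hypothesis section expects neglect to fall by 50% and motor recovery to rise by 30% compared with conventional management. Eligibility runs from 1 to 36 months after stroke.

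**The concern.** With no outcome measured during treatment, the only score available for someone who leaves before week 8 is a pre-treatment one. Carrying it forward asserts that this person did not change at all by week 8 or week 12, in a trial where both arms are treated and expected to improve. The filled-in values then enter the analysis as if they had been observed.

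Two things are at stake. If the therapy works, imputed zero changes pull the estimate towards no effect. If the arms lose different proportions, the arm that loses more is credited with less improvement whether or not the therapies differ, so a difference can be created or hidden. The protocol cannot control how losses divide between the arms. Analysing participants as randomised does not require this imputation.

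**Working it through.** **Inputs from the protocol.** Box 1 in the Sample size section gives "Mean difference = 8.6" and an SD of 10.6 for the Line Bisection Test, so the standardised effect is 8.6 / 10.6 = 0.81 SD. The error rates are "Considering the beta = 0.1 and α = 0.05". Sidedness is not stated, and two-sided is taken here. Allocation is 1:1, with 43 enrolled per group and 15% planned loss.

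**Inputs assumed.** The protocol does not give the mean control-arm improvement c, the split of losses between arms, or the correlation between baseline and outcome. The ranges used are:
- c of 0.5 and 1 SD
- losses of 15%/15%, 10%/20%, 20%/10% and 5%/25% (experimental/control)
- correlation of 0.6

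Dropout is random within each arm and, unless stated otherwise, happens before week 8.

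**The plan's own figures.** The step from 37 to 43 reproduces: 37 × 1.15 = 42.6, rounded up to 43 (dividing by 0.85 gives 44). The 37 itself does not follow from Box 1, which gives 32 per group by the normal formula and 33 by the t distribution. That is a separate matter. It leaves some spare power but does not affect the bias.

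**Formula.** Let D be the true difference in improvement, and dE and dC the proportions lost before week 8. Each lost participant contributes zero change, so

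expected carried-forward difference = (1 − dE)(c + D) − (1 − dC)c = (1 − dE)D + (dC − dE)c.

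The first term dilutes the effect. The second term vanishes when losses are equal, and otherwise has the sign of dC − dE.

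**Equal 15% loss, Box 1 scale.** 0.85 × 8.6 = 7.31, a bias of −1.29 (−15%), whatever c is. With SD 10.6, no covariate gain and the normal approximation, power is 0.892 for a difference of 7.31 with 43 per group. For 8.6 with 37 observed per group it is 0.937. If D = 0 the expected difference is 0.

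**Unequal loss, true effect 0.81 SD, c = 0.5 SD.**
- 20%/10%: 0.80 × 1.31 − 0.90 × 0.50 = 0.598, about 26% too small.
- 10%/20%: 0.90 × 1.31 − 0.80 × 0.50 = 0.779, about 4% too small.

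**Unequal loss can also exaggerate.** On the Box 1 scale with c = 8.6, 5%/25% loss gives 0.95 × 17.2 − 0.75 × 8.6 = 9.89 against a true 8.6. The reverse split gives 0.75 × 17.2 − 0.95 × 8.6 = 4.73.

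**No true effect.** The spurious difference is (dC − dE)c. Type I error was simulated with baseline-adjusted ANCOVA, 43 per arm and a nominal 5% level:

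| Loss (exp./control) | c | Spurious difference | Type I error, carried forward |
|---|---|---|---|
| 15%/15% | 0.5 SD | 0 | about 5% |
| 10%/20% | 0.5 SD | 0.05 SD | about 6–7% |
| 5%/25% | 0.5 SD | 0.10 SD | about 9% |
| 10%/20% | 1 SD | 0.10 SD | about 8.5% |
| 5%/25% | 1 SD | 0.20 SD | about 20% |

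In the same settings, ANCOVA on the observed scores recovered 0.81 SD where there was an effect and rejected in about 5% of null trials.

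**Timing of loss.** If half of the losses come after week 8, the week-8 estimate under 15%/15% loss is 0.81 × (1 − 0.075) = 0.75 SD. Type I error at week 8 under 10%/20% loss is then about 5.1% (c = 0.5 SD) or 6.3% (c = 1 SD).

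**The case against.** The strongest defence is that the scenario the protocol plans for does little harm. The 15% allowance applies to both groups, the arms have the same session load, and nothing in the document predicts unequal loss. Under equal loss the test keeps its 5% level, the bias is towards no effect, and power of about 0.89 is close to the planned 0.90. This stands, and it limits how much weight the point can bear.

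Three stronger readings are tempting, and the protocol does not support them.

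- A reader might infer that every dropout is given zero recovery. That is true only before week 8. Someone lost between weeks 8 and 12 keeps the week-8 score and is assumed only not to change further.
- A reader might infer that the false-positive rate is inflated as planned, perhaps to 20%. That figure needs both a fivefold imbalance in loss and 1 SD of recovery, and the protocol states neither. Recruitment extends to 36 months after stroke and the protocol stresses chronic stroke, so recovery may well be smaller.
- A reader might infer that analysing observed scores is free of bias. The simulations used random dropout, where that analysis is unbiased by construction. If dropout depends on the unseen outcome, it can be biased too. Participants with no post-baseline score contribute no outcome to it.

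The defence does not show that carrying forward is reliably conservative. Heavier loss in the control arm favours the experimental therapy.

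**Conclusion.** The point holds within limits. The protocol itself fixes the method, so this is not a detail left to an analysis plan, and the measurement schedule makes zero change the imputed result for anyone lost before week 8. Under the planned equal loss the cost is a dilution of about 15% with a valid test. Under unequal loss the direction depends on which arm loses more, and the size depends on recovery. At 0.5 SD recovery the inflation of type I error is modest to moderate, and it becomes serious only with larger recovery and marked imbalance.

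The dilution under equal loss needs only the stated 15% and loss before week 8. All other sizes rest on assumed recovery, loss split, correlation and random dropout within arm. A larger sample would not remove the bias.

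**What to change.** For the continuous outcomes, replace carrying forward as the primary method with a likelihood-based mixed model for repeated measures on all observed 8- and 12-week scores, with baseline score, group, visit and group-by-visit. State that it assumes data are missing at random. This keeps the planned baseline adjustment and repeated-measures structure without filling in missing visits.

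Add a delta-adjusted sensitivity analysis covering every randomised participant, including those with no post-baseline score. In it, imputed outcomes are made worse by stated amounts to see when the conclusion changes. Keep carrying forward only as a labelled sensitivity analysis. Try to assess participants at weeks 8 and 12 even if they stop attending sessions.

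The Functional Ambulation Category and modified Rankin scale are tabulated as categories. They lie outside this model and need their own stated rule.

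The cost is a few sentences of wording and a little more analysis work, with no extra participants or visits. Mixed models run in the SPSS version already named. The downside is reliance on the missing-at-random assumption, which the delta adjustment is there to test.
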